##### Strategies to improve adherence to interventions {11c}

No specials provisions will be put in place to improve adherence, besides those already carried out in usual care.

##### Relevant concomitant care permitted or prohibited during the trial {11d}

No restrictions regarding concomitant care were enacted during the trial. The only limitations were those imposed by usual care: concomitant synthetic DMARDs were allowed, corticosteroid dosage could be modified as required, intraarticular corticosteroid injections were allowed.

##### Provisions for post-trial care {30}

All patients will return to standard care after the trial.

### Outcomes {12}

#### Primary outcome measures

##### *Clinical primary outcome measure*

Therapeutic response (time frame: 6 months)

The therapeutic response will be assessed using the EULAR response criteria [24] at 6 months, which is defined by a low disease activity (DAS28-ESR < 3.2) and a decrease in the DAS28-ESR > 1.2 points from baseline (further details regarding disease activity in the “Clinical secondary outcome measures” section).

#### Secondary outcome measures

##### *Pharmacoeconomic secondary outcome measures*

Incremental cost utility ratio at 6 months (time frame: 6 months)

This outcome will be calculated as the average differential cost per patient between both study arms (mean costs of the SinnoTest® arm − mean costs of the control arm) divided by the difference in effectiveness between both study arms measured in the number of years of life weighted by the quality of life (QALY: quality-adjusted life year) generated by each of the strategies (mean QALY of the SinnoTest® arm − mean QALY of the Control Arm).

QALY will be measured using the EuroQol-5D-5L. The Spanish value set will be used to obtain the EQ-5D index values. Cost will be considered from a Societal perspective, including both direct and indirect costs The ratio will be expressed in cost (2019 Euros) per QALY earned, which represents the additional cost that will have to be spent to earn a healthy year of life.

As direct costs, we will consider concomitant medications, procedures, outpatient consultations (both primary and specialized care), hospitalizations, and complementary test (laboratory, radiology…). Regarding indirect costs, we will consider sickness absences, transportation, home assistance (both by professional and non-professional caregivers), and home modifications related to the disease.

Regarding the determination of unit costs, we will favor, where possible, a cost-of-production approach:
The prices of drugs dispensable through pharmacies will be obtained from the Database of the Spanish Official College of PharmacistsThe prices of hospital dispensing drugs will be obtained from the Pharmacy Services of each participating center.The costs of the different medical acts (first visits or revisions, in primary or specialized care, by different medical professionals) will be provided by each participating center.The costs of hospitalizations and the procedures that are carried out will be provided by each participating center.The costs of the complementary tests will be obtained from each participating center.The use of home assistance will be evaluated based on a standard average cost. The cost of employing professionals from the medico-social sector (for example, occupational therapist) will be estimated based on an average cost per hour.The cost of improvements in the home will be estimated, as far as possible, in the billing data or in the data obtained by the professionals of the sector involved.In relation to the costs of caregivers (non-professionals) and the loss of production of the patient, according to the recommendations, the direct costs will take into account the time of the people intervened and the time that the caregivers dedicate to the care of the patients. However, in relation to the valuation method, there is no agreement on the method to be used. We will favor the human capital method, where the “value” of an individual is estimated by its productive value in the labor market, that is, through the gross salary. These productive costs will be obtained through the data of age, sex, and professional sector of the individual through the national statistics available on the Spanish Social Security website.The cost of medical transport will be assessed through the rates established based on the distance and type of vehicle.

We consider that 6 months is enough time to assess the performance of the intervention. According to the EULAR recommendations for biotherapy management in rheumatoid arthritis [25], 6 months is the time to assess if the therapeutic objectives of the medication has been achieved (remission or at least low disease activity). Based on those recommendations, if the patient is still active, treatment should be modified.

Incremental cost-effectiveness ratio at 6 months (time frame: 6 months)

##### *Clinical secondary outcome measures*

Disease activity, quality of life, and disability (time frame: 6 months)

RA disease activity will be evaluated using both the DAS28-ESR and CRP indexes. They are composite scores derived from 4 measurements: number of swollen joints (out of 28), number of painful joints (out of 28), global assessment by the patient of RA activity on a scale visual analog of 0 to 10 cm (0 = no manifestation of RA, 10 = maximum severity that the patient can imagine), and either erythrocyte sedimentation rate (ESR, in mm/h) OR C-reactive protein (in mg/dL). Quality of life will be measured with the EQ5D-5 L. Disability will be measured using the Health Assessment Questionnaire (HAQ).

Software’s predictive model performance (Time Frame: 6 months)

Sensitivity, specificity, and positive and negative predicted values of the predictive models using the biomarkers will be assessed on the new clinical data from the 6-month trial.

##### *Proteomic secondary outcome measures*

Description of the variation of the proteomic profile between M0 (biotherapy start date) and M6 (6 months visit) (time frame: inclusion and 6 months)

Based on shotgun and semi-quantitative proteomics, the differences between the proteomic profile at baseline and at M6 will be analyzed.

### Participant timeline {13}

This study will be conducted by rheumatologists who have the opportunity to follow patients with RA and to conduct this study in good conditions and in accordance with regulatory and legal recommendations. The only difference in follow-up between the 2 groups is the addition of the “SinnoTest® Protein Biomarker” assay and the use of the results of this assay for therapeutic management.

Patients will be seen as part of their follow-up consultation in the Rheumatology department:
-Screening: verification of the eligibility criteria.-Inclusion or M0 visit: after information and signature of informed consent. All patients will have a SinnoTest® blood sample. At the end of this visit, the patient is randomized to the SinnoTest® group or the control group. In the control group, the SinnoTest® sample is kept but not analyzed.-6–10 days after the consultation, the prescription of the biotherapy recommended by the rheumatologist is sent by post. This prescription uses SinnoTest® results in the SinnoTest® arm.-Followed quarterly: M3 and M6.

As part of the proteomics substudy, for those patients who agree to participate, blood samples will be collected from the 2 groups in the M0 and in the M6 to study the variations in the proteomic profile of the patients. In addition, the remaining samples will be deposited in a biobank (in the recruitment center and in the Biobank of the Center Hospitalier Universitaire Grenoble Alpes, France). The participant timeline is presented in Table 1.

**Table 1 Tab1:** Schedule of enrollment, interventions, and assessments

Visits	Selection	Inclusion^a^ M0	M3 ± 2 weeks	M6 ± 2 weeks	M12 ± 2 weeks
Information^a^	✓				
Information and consent^b^		✓			
Confirmation of eligibility		✓			
Clinical/physical examination, rheumatoid arthritis		✓	✓	✓	
Routine blood analysis		✓	✓	✓	
Questionnaire EQ5D		✓	✓	✓	
Questionnaire HAQ		✓	✓	✓	
Biomarkers^c^		✓			
Patient booklet^d^		✓	✓	✓	✓
Administration/dispensation of biotherapy^e^		✓			
Biobank^f^		✓		✓	
Concomitant treatments		Collection throughout the study			
Adverse effects collection		Collection throughout the study			

^a^ Inclusion: The inclusion visit should be done in 2–3 weeks

^b^ Information and informed consent: The patient will sign informed consent for the main study and additional consent (optional) if they accept 6-month and 1-year inclusion samples, which will be retained for the creation of biobank

^c^ Biomarkers: A blood sample will be taken for the determination of SinnoTest® biomarkers in the intervention arm patients

^d^ Patient booklet: The rheumatologist or CRA investigator will deliver the booklet to the patient at the inclusion visit. The patient brings the notebook during each follow-up visit and will carry it with him after the visit. At the end of the follow-up, he will return his completed patient booklet to the CRA / TEC of the Investigator Center by mail using the envelope provided with the notebook

^e^ Administration/dispensation of biotherapy: Patients in the control group will receive their biotherapy prescription in current practice. For patients in the intervention group, the rheumatologist will prescribe the biotherapy selected by SinnoTest®. The results of the pregnancy test should be negative

^f^ Biobank: A blood test will be carried out in all included patients who signed the additional consent for the creation of a biobank

### Sample size {14}

To re-evaluate the metrological properties of SinnoTest®, including 90 patients per group will highlight a differential response rate between the software arm and the control arm of more than 18.2%, considering a current response rate of 65% (defined as an EULAR good response [24]) with conventional care (control arm). The number of subjects required was estimated considering a bilateral alpha risk at 5% and a power of 80%. In total, 180 patients will be the estimated number of participants needed to achieve study objectives.

Due to the subject’s and the study’s characteristics, no allowance for loss to follow-up was considered in the sample size calculation: patients with a chronic disease, probably being followed up in the same center and by the same rheumatologist for some time (> 1 year), and the short follow-up time for the primary outcome.

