## Abstract

**Background:**

Rheumatoid arthritis (RA) is one of the leading chronic inflammatory rheumatism. First-line therapy with synthetic disease-modifying antirheumatic drugs (sDMARD) is insufficiently effective in 40% of cases and these patients are treated with biotherapies. The increased use of these drugs each year is becoming a public health issue with considerable economic burden. This cost is 20 times higher than that of sDMARD. However, among patients treated with biotherapies, clinical practice shows that about one third will not respond to the selected drug. In nonresponse cases, practitioners currently have no choice but to perform an empirical switching between different treatments, because no tool capable of predicting the response or nonresponse to these molecules is currently available.

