One of the major current challenges in RA management is being able to predict drug responsiveness before treatment initiation [5], as there are no tools able to predict the response to a particular medication [6]. Rheumatologists lack evidence-based knowledge to choose the most suitable DMARD for their patients, and these drugs are prescribed in a “trial-and-error” manner. In case of a lack of response (which has been reported around 30–50% for bDMARDs [3, 7]), the physicians have to perform an empirical rotation between the different drugs, until the correct drug, or combination of drugs for this particular patient is found. Therefore, nonresponders are unnecessarily exposed to undesired adverse events along with the worsening of their physical condition. Furthermore, the ineffective use of bDMARDs has a dramatic economic burden due to their important costs [4]. A study by Meissner and colleagues [8] shows a greater overall economic impact on the health system of patients who changed bDMARD following failure of a first biological compared to those who did not change. This economic burden is even greater when the patient has to change his/her treatment for a second time. This phenomenon seems difficult to reverse in case of initial misdirection, since the probability of a patient who has already received an anti-TNF to respond to another biological treatment decreases gradually according to the increasing number of failures of previous treatments [9]. A tool able to provide a probability score of response or nonresponse to specific treatments could pose an important benefit for clinicians and patients.

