##### Criteria for discontinuing or modifying allocated interventions {11b}

The discontinuing or modifying allocated interventions for a given trial participant in the study will be as follows: lack of response to medication in the intermediate visit (3 months after inclusion) using the EULAR response criteria; occurrence of adverse events, including malignancy; loss to patient follow-up; withdrawal of consent by the patient; decision of the investigator (inadequate follow-up of the instructions of the doctor or study staff); the rheumatologist or the promoter (medical monitor) decides that continuing the study can be harmful to the patient; in case of pregnancy (only if the patient is under treatment with a therapy that does not recommend pregnancy; in the event that the medication is compatible with the pregnancy, the patient can still be included in the study); in case the patient needs a treatment or has received some treatment not allowed in the study; erroneous inclusion in the study; circumstances not foreseen; cancelation of the study.

Patients discontinuing the intervention will not be followed up and will be withdrawn from the study.

No treatment / procedure prohibited during the study.

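### The stated 80% power assumes a 6-month outcome from all 180 patients, but the withdrawal rule removes that outcome from patients who discontinue, including for non-response at month 3

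*Protocol article*

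**What the plan says.** All references are to the protocol article.

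- **Sample size {14}.** The design claim is that "including 90 patients per group will highlight a differential response rate between the software arm and the control arm of more than 18.2" percentage points, "considering a current response rate of 65% (defined as an EULAR good response"), with "bilateral alpha risk at 5% and a power of 80" per cent. On attrition, "no allowance for loss to follow-up was considered in the sample size calculation". The reasons given are that the disease is chronic, that patients probably stay with the same centre and rheumatologist, and that follow-up to the primary outcome is short.
- **Criteria for discontinuing or modifying allocated interventions {11b}.** The listed grounds include lack of EULAR response at the 3-month visit and adverse events. The section ends: "Patients discontinuing the intervention will not be followed up and will be withdrawn from the study".
- **Plans to promote participant retention {18b}.** Participants are to be taught why research follow-up matters even if they stop the study drugs.
- **Outcomes {12}.** The primary clinical outcome is EULAR response at 6 months: DAS28-ESR below 3.2 with a fall of more than 1.2 from baseline.
- **Non-adherence and missing data {20c}.** Analysis is by intention to treat, and multiply imputed data are used for the primary and secondary outcomes.
- **Response rates elsewhere.** The abstract says "about one third will not respond to the selected drug". Background and rationale {6a} gives lack of response, "which has been reported around 30–50% for bDMARDs", and adds that the chance of response declines as previous failures accumulate.

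**The concern.** The zero-loss reasoning addresses patients drifting out of contact. It does not address withdrawal that the protocol itself prescribes. A patient withdrawn at or soon after M3 for non-response has no observed M6 DAS28-ESR, so the primary outcome is missing because treatment failed. The retention section points the other way, and the two cannot both be followed.

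Two things are at stake. First, a neutral result could be read as coming from an 80%-powered trial when the information behind it was smaller. Second, missingness that depends on response, and hence possibly on arm, can bias the comparison as well as weaken it.

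A secondary question is whether 65% good response is a safe control rate for patients who have all failed one anti-TNF.

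**Working it through.** **Inputs.** From Sample size {14}: p1 = 0.65, difference 0.182, so p2 = 0.832; two-sided alpha 0.05 (z = 1.960); power 80% (z = 0.842); 90 per arm; no loss. Allocation is 1:1 (Implementation {16c}).

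**Step 1: reproduce the plan's figure.** Pooled two-proportion formula, no continuity correction:

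n = [1.960 × √(2 p̄(1 − p̄)) + 0.842 × √(p1(1 − p1) + p2(1 − p2))]² / (p2 − p1)²

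With p̄ = (0.65 + 0.832)/2 = 0.741:

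- 2 × 0.741 × 0.259 = 0.3838, square root 0.6196
- 0.65 × 0.35 + 0.832 × 0.168 = 0.2275 + 0.1398 = 0.3673, square root 0.6060
- n = (1.2143 + 0.5101)² / 0.0331 = 89.8, rounded up to 90

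The plan's 90 per arm is confirmed. Power at exactly 90 per arm is 80.1%, so nothing is in reserve.

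**Step 2: power when some M6 outcomes are missing (observed cases).** Power = Φ[(0.182 − 1.960 × SE0)/SE1], where SE0 is the pooled standard error and SE1 the unpooled one. At 81 per arm, SE0 = 0.0688 and SE1 = 0.0673, giving Φ(0.70) = 0.758. The loss rates below are assumptions, because the document states none.

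| Assumed missing, both arms | Outcomes per arm | Power |
|---|---|---|
| 0% | 90 | 80.1% |
| 5% | 85.5 | 78.0% |
| 10% | 81 | 75.8% |
| 20% | 72 | 70.7% |

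**Step 3: loss tied to the plan's own response rates.** At the planned rates, 35% of controls and 16.8% of the SinnoTest arm do not reach good response.

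- All of them withdrawn: 90 × 0.65 = 58.5 and 90 × 0.832 = 74.9 outcomes remain (about 58 and 75). Nominal power is 67%.
- Half of them withdrawn: 90 × 0.825 = 74.3 and 90 × 0.916 = 82.4 remain. Nominal power is 74.5%.

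These are precision figures only: they hold 65% and 83.2% fixed while shrinking the arms. In the first case the patients left would all be good responders in both arms, so an observed-case comparison would show no difference at all. That is why bias matters here as well as power.

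**Step 4: control rate.** The complement of 30–50% non-response is 50–70% response, and the complement of one third is about 67%. Holding 90 per arm fully observed and the difference at 18.2 points:

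| Control rate | Power |
|---|---|
| 50% | 70.3% |
| 60% | 75.7% |
| 65% | 80.1% |
| 70% | 85.8% |

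**The case against.** **Imputation and follow-up soften the loss.** The plan is intention to treat with multiple imputation, M3 clinical data are scheduled, and the retention section encourages follow-up after stopping study drugs. The observed-case figures are therefore not the power of the planned analysis, and it would go too far to say that the trial simply lacks its stated power. This stands as a limit on the size of the problem, but does not remove it. The retention text conflicts with the withdrawal rule; imputation recovers only part of the information; and no rule says how a patient withdrawn for M3 non-response is treated in the primary analysis.

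**The loss rates are not in the document.** Correct, and they are labelled as assumptions. The M3 trigger is lack of EULAR response, which is narrower than failing to reach good response, and the section covers modification as well as discontinuation. So the 67% figure is an outer case for withdrawal through non-response alone. Pooled non-good-response at the planned rates is (35 + 16.8)/2 = 25.9%, so much heavier losses could not come from non-response alone.

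**A reader might infer that the non-response figures contradict the 65%.** They do not: 65% lies inside 50–70% and close to 67%. Nor does 80% power require exactly 65%, since a 70% control rate gives 86%. It is also tempting to argue that 65% is really an any-response rate mislabelled as good response, and that the true rate is well below 50%. The document does not define response in those two places and gives no figure for the decline after previous failure, so it supports no such number.

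**Conclusion.** The concern holds for the zero-loss assumption. The sample size arithmetic is right, but its 80% depends on complete M6 outcomes, while the plan's own rule withdraws patients who discontinue, including for M3 non-response or adverse events, without further follow-up. On observed cases, power falls to about 78, 76 or 71% with an assumed 5, 10 or 20% missing. With the plan's response rates it is nominally about 67% if every patient without good response were withdrawn and 74–75% if half were. How much imputation would win back cannot be determined from the document, and the response-dependent missingness carries a risk of bias that these figures do not measure.

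The control-rate point is secondary and weaker. The 65% is compatible with the document's figures, but those figures are not said to use the good-response definition, and the background says response falls after earlier failures. It may be optimistic; it is not shown to be wrong. Over the document's own range, power for 18.2 points runs from 70% to 86%.

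**What to change.** Keep 180 patients and reconcile sections {11b}, {14}, {18b} and {20c}.

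1. **Preferred:** state that the M6 DAS28-ESR outcome is collected in all randomised patients, whether or not the biotherapy is discontinued. This separates stopping treatment from leaving the study and changes no clinical rule for stopping.
2. **If withdrawal stays:** state in the primary analysis section how patients withdrawn for M3 non-response enter the primary analysis, and amend the imputation text to agree. Such a rule should not be introduced inside the sample size paragraph.
3. **In Sample size {14}:** replace the zero-loss statement with, for example: *With 90 per arm and 65% versus 83.2% good response, power is 80% if all M6 outcomes are observed and about 78, 76 and 71% on observed cases if 5, 10 or 20% are missing; these rates are assumptions.*
4. **Control rate:** give the source of the 65%, with its response definition and patient population, and report power for an 18.2-point difference at control rates of 50, 60, 65 and 70% (about 70, 76, 80 and 86%).

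Cost: the stated power becomes somewhat less favourable and, under option 1, M6 visits continue for patients who have stopped the biotherapy. No extra patients are needed.

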### Recruitment {15}

Recruitment will be done among patients coming for rheumatology consultations in the 5 centers participating in the study. Potentially eligible patients will be identified in the everyday clinical practice of the research staff, or referred to them for assessment of eligibility having been identified by rheumatologists who are not research staff. Medical records will be checked to identify any other potentially eligible patients. The patient’s eligibility will be confirmed by the responsible researcher. After confirmation, any patient who agrees to participate in the research must sign the informed consent to begin participation.

### Assignment of interventions: allocation

#### Sequence generation {16a}

It was centrally generated at the Hospital Clínico San Carlos Clinical Research Unit.

